## **5 STUDY INTERVENTIONS**

### **5.1 Overview**

The exercise interventions will be delivered in 2 phases. The first phase or 12 week class will be delivered by the exercise leader. The second phase or 12 week class will begin once the first phase is completed and will be delivered by staff activity personnel. Participants who are randomized to the second phase class (i.e. delivered by staff activity personnel) will repeat the baseline testing prior starting the exercise class.

The facilities will be randomized (described above) to receive either the "On the Move" or a standard group exercise program. Both exercise programs (On the Move and standard) will be group-based and led by a person. Both programs will be delivered by trained exercise leaders or trained staff activity personnel (sustainability component). The frequency and duration of the programs are identical (50 minutes, 2 times a week for 12 weeks). From our past research we have determined that a frequency of 2 times per week for 12 weeks is acceptable to the older adult participants and is an adequate dose to obtain meaningful outcomes.(23) The main difference between the standard and the On the Move group exercise programs is the program content which is described below.

### **5.2 On the Move**

The On the Move exercise program is based on principles of motor learning that enhance “skill” or smooth and automatic movement control.(24-29) The program contains a warm-up (5 minutes), stepping patterns (15 minutes), walking patterns (15 minutes), strengthening exercises (10 minutes), and cool-down exercises (5 minutes). The warm-up and cool down contain gentle range of motion exercises and stretches for the lower extremities and trunk. The stepping and walking patterns are goal-oriented progressively more difficult patterns which promote the timing and coordination of stepping, integrated with the phases of the gait cycle.(25, 26, 28, 29) Conceptually, the exercise is intended to achieve its effects by shifting the center of pressure posteriolateral then forward, encouraging hip extension prior to stepping, loading the trailing limb, coordinating activation of the abductors of the soon to be swing leg with adductors of the stance limb, and shifting the center of pressure in medial stance to unload the stepping limb.(30-32) Progression is based on first separately increasing the speed, amplitude or accuracy of performance prior to undertaking a more complex task.(33) For example, the progression of stepping patterns is, 1) self-paced step forward and across, 2) increase stepping speed, 3) alternate side of stepping, 4) alternate forward with backward stepping. In the group class,

exercises can be individualized by having some older adults use upper extremity support while others do not hold on during the exercises. Also, some subjects will step in all one direction while others will do the more challenging alternating left and right steps. Walking patterns incorporate patterns of muscle coordination and interlimb timing into walking. Walking patterns progress by altering speed, amplitude (e.g. narrowing oval width), or accuracy of performance (e.g. without straying from the desired path), and then to complex walking patterns involving walking past others and with upper extremity object manipulation tasks, such as carrying or bouncing a ball. Walking and stepping patterns (i.e. timing and coordination training) were used in both of our pilot studies. the strengthening exercises are conducted in sitting and standing and target the lower extremity muscles. The majority of the program will be conducted in standing (40 minutes) with only a small portion conducted in sitting (10 minutes). We have conducted two pilot exercise classes with older adults with varying levels of ability. We were able to successfully individualize the group program in that participants reported feeling both challenged and safe. Please see the appendix for example exercises and progressions.

### 5.3 Standard

The standard group exercise program is based on exercise programs that are currently being conducted at the facilities (i.e. standard of care). The operationally defined program contains a warm-up (5 minutes), upper and lower extremity strength and flexibility exercises (20 minutes), cardiovascular exercises (20 minutes) and a cool-down (5 minutes). The majority of the program will be conducted in sitting (>40 minutes) with only a small portion (<10 minutes) conducted in standing. The active control group (i.e. standard exercise program) will aid in adherence and retention in that subjects who volunteer to participate in the study will be looking for exercise options.

### 5.4 Monitoring of vital signs

Vital signs will be monitored before and after the exercise class as needed. Vitals signs will be monitored more at the beginning of the program, and at any time the participant reports or displays signs and symptoms (i.e. shortness of breath, lightheadedness, racing heart, etc). We will once again follow the ACSM guidelines for stopping of exercise.

### 5.5 Program monitoring

Periodically (approximately 1-2 times) throughout the exercise program we will be videotaping the exercise sessions. These videos will be used primarily to monitor the quality and consistency of the exercise program and to further develop the training manual for the exercise instructors. The videos may be used to train future exercise instructors.

### 5.6 Adherence Assessment

A roster of participants will be developed for each group exercise class. At the beginning of each class, attendance will be recorded by the exercise leader or staff activity personnel. Reasons for missed classes will be recorded when available. Attendance rate ([number of sessions attended

544 by the participant/total number of classes offered, i.e 24] X100%) will be calculated for each  
545 participant and will be the main indicator of adherence.

546

## 547 6 **STUDY PROCEDURES**

548

549      **6.1 Schedule of Evaluations**

| Measure                                             | Clinic Screen | Baseline 1
Pre-intervention | Baseline 2
Pre-intervention
Activity staff group | 12 week
Post-
intervention |
|-----------------------------------------------------|---------------|--------------------------------|--------------------------------------------------------|----------------------------------|
| Demographics Questionnaire                          | X             |                                |                                                        |                                  |
| Physical exam screen (BP, strength, 2 step command) | X             |                                |                                                        |                                  |
| 6 MWT                                               | X             |                                | X                                                      | X                                |
| Screening gait speed                                | X             |                                |                                                        |                                  |
| Comorbidities Index                                 |               | X                              |                                                        |                                  |
| Fall history                                        |               | X                              | X                                                      | X                                |
| Anthropometric Measurements                         |               | X                              |                                                        |                                  |
| Gait Measures                                       |               |                                |                                                        |                                  |
| Gait speed – Zeno Walkway                           |               | X                              | X                                                      | X                                |
| Complex walk (Shumway-Cook)                         |               | X                              | X                                                      | X                                |
| SPPB                                                |               | X                              | X                                                      | X                                |
| Figure 8                                            |               | X                              | X                                                      | X                                |
| GES                                                 |               | X                              | X                                                      | X                                |
| Physical Function                                   |               |                                |                                                        |                                  |
| LLFDI                                               |               | X                              | X                                                      | X                                |
| Global items                                        |               | X                              | X                                                      | X                                |
| Potential confounders                               |               |                                |                                                        |                                  |
| PHQ-9                                               |               | X                              | X                                                      | X                                |
| Digit Symbol Substitution Test                      |               | X                              | X                                                      | X                                |
| Program Evaluation                                  |               |                                |                                                        |                                  |
| Satisfaction survey                                 |               |                                |                                                        | X                                |

550  
551  
552

## 6.2 Description of Evaluations

### 6.2.1 Baseline Assessments

If after the clinic screen the participant is eligible (i.e. meets all inclusion/exclusion criteria) they will undergo baseline testing. All baseline testing will be performed by research staff trained in the testing procedures. All testing will be completed at the ILFs and Senior Housing Sites.

Our main outcomes, function, disability, and walking ability are highly associated with independence and are extremely important to the older adult. Our primary measure of function and disability is the Late Life Function and Disability Instrument (LLFDI) and our main measures of walking ability are Six Minute Walk Test (6MWT) and gait speed. We will also examine confidence in walking (Gait Efficacy Scale), walking under challenging conditions (challenging gait tasks and figure of 8 walk), gait variability and the Short Physical Performance Battery (SPPB) as additional measures of walking ability. We will also collect a measure of cognition (Digit Symbol Substitution Test) and mood (PHQ-9).

#### 6.2.1.1 Function and Disability

Late Life Function and Disability Instrument (LLFDI).(35, 36) Our primary function and disability outcome will be the LLFDI. The LLFDI is a pair of self-report measures targeted for assessing physical function and disability in older adults with acute or chronic problems, and designed to be more sensitive to change than similar measures. The two components of the LLFDI correspond to the activity (LLFDI – function) and participation (LLFDI – disability) components of the World health Organization’s International Classification of Function, Disability and Health model. The LLFDI function component has 32 items in three dimensions, basic lower extremity (BLE), advance lower extremity (ALE) and upper extremity (UE) and the LLFDI disability component has 16 items representing two dimensions, frequency of performance and limitation in performance of life tasks. We’ve selected the LLFDI because 1) it measures both function and disability which are critical components of independence, 2) it includes a wide variety of life tasks in various social areas thus extending beyond the traditional focus of just activities of daily living, 3) the scale was designed with sufficient breadth of items and increments of rating in order to minimize ceiling and floor effects and maximize the scale’s ability to detect change over time, and 4) it is a continuous outcome which gives us greater power than a dichotomous outcome to detect change over time. We will focus our analyses on the LLFDI function and disability dimension scores (i.e. BLE function, ALE function, UE function, disability frequency and disability limitation). We will also examine the disability domain scores (social role, personal role, instrumental role and management role) since they may provide insight into the impact of the disability on frequency of performance and perceived limitations.(36) The LLFDI function and disability scales have established known groups validity and the test-retest reliability is moderate to high for the disability component (ICCs range from 0.68 to 0.82) and extremely high for the function component (ICCs range from 0.91-0.98 for the dimensions). Scores range from 0-100; higher scores represent less difficulty and less disability.

#### 6.2.1.2 Walking Ability

Six-Minute Walk Test (6MWT). One of the main walking ability outcomes is the Six-Minute Walk Test (6MWT) of distance walked (meters) in six minutes, including time for rest as needed.(37) We have selected the 6MWT because it is 1) a performance-based measure of walking ability and walking ability is an important component of independence, 2) an indicator of community ambulation (i.e. the ability to walk 300m in 6 minutes),(38, 39) 3) a continuous outcome which gives us greater power than a dichotomous outcome to detect change over time,(40) and 4) a widely used measure of mobility that is included in the NIH PROMIS project to establish measures of clinical assessment. The 6MWT has established psychometric properties, test-retest reliability (Pearson  $r=.95$ ) in older adults,(41, 42) construct validity for graded exercise test and functional classification.(43) The Six-Minute walk test will be completed as part of the clinic screen (described earlier) and also used as an outcome measure. Participants will only complete the 6MWT once at baseline. Participants will be asked to walk as far as they can in six minutes (without jogging or running) in a hallway. Participants are permitted to stop and rest during this test, if needed, and the number and duration of rest breaks are recorded. Blood pressure, heart rate and level of fatigue (using the rate of perceived exertion (RPE) scale) are recorded before and after the test. Based on the ACSM guidelines, subjects who have an inappropriate exercise response (i.e. exercise heart rate  $\geq 120$  bpm, exercise SBP  $\geq 220$  or a drop in SBP  $> 10$  mmHg, or DBP  $\geq 110$  mm Hg) will be referred to their primary care physician for clearance before they can be enrolled in the study.(34) Greater distance covered during six minutes is better.

Gait Speed. The second main walking ability outcome is gait speed. We have selected gait speed because it is a strong indicator/predictor of morbidity and mortality in the older adult.(2, 3, 5) Gait speed is assessed in usual walking with an instrumented walkway. After explanation, the participant completes 2 practice walks to become accustomed to walking on the walkway. The subject then completes 4 passes at their usual, self-selected walking speed. Gait speed will be averaged over the 4 passes. The test-retest reliability of gait speed measured using instrumented walkways by ICC is 0.98.(44) A faster speed is better.

#### 6.2.1.3 Additional Mobility Measures

Gait Efficacy Scale. In order to determine if changes in walking ability are associated with changes in confidence in walking, confidence will be assessed using the Gait Efficacy Scale.(45-47) The items include a range of gait activities such as walking over different surfaces, up and down curbs, and negotiating stairs. Each item has a 10 point Likert scale scoring option, with the total score for the 10 items, ranging from 0-100. A higher score represents greater confidence.

Figure of 8 Walk.(48) The Figure of 8 Walk was designed to measure motor skill in walking. The test involves walking a figure of eight pattern about two markers placed 5 feet apart. Performance is scored based on the time to complete the figure 8 walk and the number of steps. Faster and fewer steps are better.

Challenging Gait Tasks. Challenging gait tasks are used to examine an individual's ability to adapt their gait to different environmental conditions.(49)53 Subjects will complete two, 12

meter trials of each challenging condition, obstacle, curved path, and narrow path.(49) The time to complete each task, averaged over two trials, is the summary indicator of gait during challenging tasks. In a sample of 40 community-dwelling older adults, the 1-week test re-test reliability of the timed measures of challenging gait ranged from ICC = 0.70 to 0.94. The marginal additional time for completing each challenging task compared to usual gait is the main indicator and lower marginal cost is better.

**Gait Variability.** Gait variability, defined as fluctuations in gait characteristics from one step to the next,(50) is an important indicator of impaired mobility in older adults.(9) Gait variability is quantified using established measures of temporal and spatial gait characteristics including stance time, step length, and step width. Variability will be calculated as the standard deviation of the set of steps recorded over 4 passes on the instrumented walkway (described above). Approximately 32 steps will be collected from 4 passes on the mat which will be more than adequate to achieve a stable measure of gait variability. Our prior work has shown that 20 steps are sufficient to achieve a reliability of 0.75 and 30 are sufficient for 0.80.(51) In general, lower variability is better although there are exceptions.(9, 52)

**Short Physical Performance Battery (SPPB).** The SPPB of lower extremity function was designed and used in the Epidemiologic Studies of the Elderly (EPESE) to assess lower-extremity function of individuals 65 years of age and older. It combined measures of gait speed, balance, and timed chair rise to develop the SPPB for lower-extremity function. The three components are: gait speed over 4-meters, standing balance and chair stands are timed and these times are converted to scores from 0-4 (0=unable, 4=fastest time) for each component. Total scores on the Battery range from 0-12, ranges defined for relative risks of disability.(4)

#### 6.2.1.4 Cognition and Mood

**Digit Symbol Substitution Test.**(53)A measure of processing speed, the Digit Symbol Substitution test will be used to gather information about both motor and cognitive processing speed. The DSST is a paper and pencil task from the WAIS III that provides normed measures of both motor and cognitive processing speed. The DSST has been widely used in studies of physical and cognitive performance of older adults.

**Patient Health Questionnaire (PHQ-9).**(54) The PHQ-9 is the 9 item depression scale of the Patient Health Questionnaire. It asks participants to describe how they have been feeling over the past 2 weeks. It has been used successfully in older adults.

#### 6.2.2 Baseline 2 Assessments

Individuals who are randomized to the second exercise session taught by the staff activity personnel (or by the exercise leader if staff person not ready to lead it) will complete a second baseline assessment prior to initiating the exercise class. This will be approximately 12 weeks after the initial baseline assessment. Baseline 2 Assessment will be identical to Baseline testing.

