### 6.2.3 Post-Intervention Assessment

At the completion of the 12 week exercise program, all participants will undergo a post-intervention assessment. The assessment will include all measures from the baseline assessment (LLFDI, 6MWT, gait speed, Gait Efficacy Scale, walking under challenging conditions (challenging gait tasks and figure of 8 walk), gait variability, SPPB, DSST, PHQ-9. Post-intervention testing will be completed at the sites (ILFs and senior housing sites) by research personnel masked to the intervention group and trained in the testing procedures.

In addition, we will also assess participant satisfaction. Participant satisfaction will be assessed using in-depth interviews and a satisfaction survey. In-depth phone interviews will be used to assess satisfaction in a subsample of participants (approximately 20%). We will randomly select a diverse sample of older adults representing the different intervention arms (On the Move, Standard, exercise leader, activity staff personnel) and the different sites (ILF and senior housing). We selected in-depth interviews instead of focus groups because we are more likely to draw people out, they are less intimidated, and more likely to be truthful. The interview will be developed by The Evaluation Institute under the direction of [name] (Co-Investigator) and with input from the other investigators and stakeholders (Community Advisory Board). The interview will include a mixture of closed and open-ended questions. Sample topics to be included in the interviews include perceived benefits and risks, satisfaction with the program, facilities, and instructor, and amount of individualized instruction. The interview will be pilot tested and modified accordingly prior to administration in the study. Pilot testing will ensure that the questions are understandable to our target population and that we are obtaining the information and feedback that we hope to obtain.

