#### **7.5 Adverse Events and Serious Adverse Events**

If an adverse event occurs during testing or intervention, staff or activity personnel will assess the situation and provide immediate assistance to the participant if necessary. If a medical emergency should occur, staff will immediately contact 911. They will describe the incident to the 911 operator and provide their location. They will also contact the facility director to make them aware of the situation. In each testing/exercise space, we will post a copy of the emergency plan which will include the number to call (911) and the address of the facility. All staff will be informed of the emergency procedures prior to starting the interventions and they will be reviewed every 6 months. Once the emergency situation is under control, the staff will contact the study PI to notify them of the situation. The PI will report unexpected or adverse events in accordance with the University of Pittsburgh IRB guidelines. As a group the PI and Co-Is review the adverse events to determine if they are expected vs unexpected and serious vs not serious. All events are reported to the irb who will also review the events. The study coordinator ([name]), study biostatistician ([name]) and study physician ([name]) who are unblinded will track the events to determine if there are an unequal number of events between the groups.

A clinical complication form will be completed any time an incident (accident, injury, illness, problems with medication, etc.) occurs or a subject reports an episode. Complications will be categorized as study related, possibly study related, or not study related. Any complications that are categorized as either study related or possibly study related will be reported to the IRB per protocol if the event is an unexpected event, and/or is of serious or moderate to severe in nature as defined by the IRB. A separate clinical complication form will be completed for each incident that may occur in each subject. The form will be kept in the subject's research record.

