## 9 STATISTICAL CONSIDERATIONS

### 9.1 General Design Issues

A randomized trial is needed to control for confounding factors that affect the outcome. There are no ethical issues regarding a randomized trial since both groups will be receiving an active exercise intervention delivered by trained personnel. We carefully considered the advantages and disadvantages of randomizing at the level of the facility and the resident. Given the amount of interaction that occurs between subjects within a facility, it is imperative that we conduct a cluster randomized trial, and randomize by facility to exercise programs. If we randomize at the resident, participants would discuss details of their intervention and cause cross-contamination between the intervention arms. Unlike a traditional trial in which participants are randomized as they are being recruited, a cluster randomized trial also affords the additional benefit of examining the facility characteristics such as type (independent living/senior high rise) and size, and ensuring a balance in those characteristics is achieved by design rather than chance. Once the facilities are randomized to exercise program, we will then randomize within facility for delivery mode (i.e. subjects will be randomized to either an exercise leader or staff activity person led exercise program). Randomization for delivery mode will occur after baseline testing. We will use a commercially available high quality pseudo-random deviate generator such as that available in SAS® (SAS Institute, Inc., Cary, North Carolina) known to be free of serial correlations(56) to randomize facilities to the two arms in a 1:1 ratio, stratified by facility type. In addition, the proposed design reaps the advantages of a paired comparison for the exploratory hypothesis (Aim 2) as both exercise leaders and staff activity personnel will be delivering On the Move in the same set of facilities, where feasible to train a staff person ready to lead the class safely and per protocol.

The main outcomes are self-reported function and disability (Late Life Function and Disability Index/LLFDI) and walking ability (6-minute walk test/6MWT and gait speed). We will also examine satisfaction, attendance rates and adverse event (falls, soft tissue injuries, muscle soreness, etc) rates.

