#### 9.3.3 Aims 2, 3(b) and 4 exploratory Analyses

##### Aim 2:

We propose an analytic strategy with an exploratory philosophy for Aim 2 sustainability aim, because of the uncertainty surrounding our ability to recruit and train a staff activity person to lead a class safely and per protocol.

We will fit a series of linear mixed models using the SAS® MIXED procedure with baseline to follow-up change in each of the continuous outcomes (LLFDI function/disability, walking ability, other measures of mobility performance) as the dependent variable; intervention arm (standard/*On the Move*), delivery mode (by exercise leader/staff activity personnel) and their interaction as fixed effects of interest; baseline value of outcome and any other measures found to be different between arms or deemed important as additional fixed effects covariates; and a facility random effect to account for greater similarity of participants from the same facility compared to different facilities and resulting non-independence of observations within facility (ie. clustering). We will construct appropriate means contrasts to estimate difference in gains in the two interventions when delivered by staff exercise personnel (Aim 2 effectiveness hypothesis); and difference in gains attributable to *On the Move* intervention when delivered by exercise leaders and staff activity personnel (Aim 2 sustainability hypothesis). Statistical significance of the estimates will serve as formal tests hypotheses. We note that participants randomized to staff activity personnel had to wait 12 weeks since their baseline assessment and randomization to start the intervention, during which they may have changed; and that they underwent a second baseline assessment immediately prior to starting the exercise intervention. Therefore, we will repeat the above analysis using their second baseline assessment instead of the first one to assess the sensitivity of results.

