## 10 DATA COLLECTION AND QUALITY ASSURANCE

### 10.1 Data Collection Forms

Data collection will consist of paper forms. Data collected on paper forms will be entered into the electronic database by the research staff.

Screening and baseline data collection, which will occur prior to randomization, will be conducted by research staff trained in the outcomes and may include the study coordinator if necessary. Outcome assessments post-intervention will only be conducted by research staff trained in the outcomes and who are blinded to the intervention group assignment.

1205 Participants' confidentiality will be protected in the data collection process. All study personnel  
1206 are certified in Research Practice Fundamentals, Human Subjects Research Module. Consent  
1207 forms and paper data collection forms will be stored in locked file cabinets. All computers are  
1208 password protected. Only authorized team members will have access to personal information  
1209 needed for tracking and informed consent.

1210

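### Baseline 2 is measured about 12 weeks after delivery-mode randomisation, but the plan does not require masked testers for it

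*Supplement*

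**What the plan says.** All references are to Protocol Version 2.0.

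- **Order of events.** Section 9.1: "Randomization for delivery mode will occur after baseline testing". Section 6.2.2 places Baseline 2 about 12 weeks after the first baseline, for everyone in the second class, and adds "Baseline 2 Assessment will be identical to Baseline testing".
- **Who may test at baseline.** Section 10.1: "Screening and baseline data collection, which will occur prior to randomization, will be conducted by research staff trained in the outcomes", and this staff "may include the study coordinator if necessary". Section 6.2.1 likewise asks only for training.
- **Who may test after the class.** Section 10.1: "Outcome assessments post-intervention will only be conducted by research staff trained in the outcomes and who are blinded to the intervention group assignment". Section 6.2.3 agrees: testing is "by research personnel masked to the intervention group and trained in the testing procedures".
- **Status of the coordinator.** Section 7.5 names the study coordinator, biostatistician and physician as the people "who are unblinded will track the events to determine if there are an unequal number of events between the groups".
- **Use of Baseline 2.** For participants in staff-led classes, the Aim 2 text in 9.3.3 says "we will repeat the above analysis using their second baseline assessment instead of the first one to assess the sensitivity of results". The Aim 1 text in 9.3.2 adds a sensitivity analysis with a third, wait-list arm made up of people waiting for the second class.

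**The concern.** Baseline testing is commonly left unmasked because nobody has yet been allocated. That reasoning fails for Baseline 2. Delivery mode has been assigned, and the facility's first class, in a known programme, has just run its 12 weeks. Baseline 2 is nevertheless tied to the baseline rule, which permits an unblinded tester.

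A tester who knows the allocation can influence the result through encouragement or timing. Of the main outcomes, the 6MWT is probably the most exposed, since the LLFDI is self-report and gait speed is read from an instrumented walkway. The two sensitivity analyses that use Baseline 2 are meant to check robustness. If one side of each is measured without masking and the other side with it, a difference, or the lack of one, may partly reflect who did the testing.

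**Working it through.** No power or sample-size figure bears on this, so the check consists of rebuilding the visit order and following Baseline 2 into the analyses.

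**1. Visit order for a second-class participant** (sections 5.1, 6.2.2, 9.1, and Aim 2 in 9.3.3)

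- Week 0: screening and Baseline 1, then randomisation to delivery mode
- Weeks 0 to 12: waiting, while the first class runs in the same facility
- About week 12: Baseline 2
- Next 12 weeks: second class, then the post-intervention test

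Baseline 2 therefore comes about 12 weeks after randomisation.

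**2. Which tester rule applies**

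Section 10.1 has two classes of visit.

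- Screening and baseline: described as pre-randomisation, trained staff, coordinator allowed. The description is untrue of Baseline 2, but 6.2.2 points to this class.
- Post-intervention: masked staff only. Baseline 2 is not named here.

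No other section assigns a tester to Baseline 2. The single-blind label in sections 3 and 12 does not say which visits it covers.

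**3. Where the measurement goes**

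Let *s* be an average shift in a Baseline 2 score caused by an unmasked tester. The models take change as the outcome and adjust for baseline. If *b* is the slope of follow-up on baseline, a shift *s* in one arm's baseline moves that arm's adjusted gain by −*b* × *s*.

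- *Aim 2 sustainability contrast, repeated with Baseline 2* (On the Move, staff-led against leader-led): the staff-led arm uses Baseline 2 and the leader-led arm uses Baseline 1. The shift enters one side only and does not cancel.
- *Aim 2 effectiveness contrast, repeated with Baseline 2* (staff-led On the Move against staff-led Standard): both sides use Baseline 2. A common shift gives −*b* × *s* − (−*b* × *s*) = 0. Only a shift that differs by programme remains.
- *Aim 1 three-arm sensitivity analysis*: the schedule in 6.1 has no other assessment at the end of the wait, so Baseline 2 is by inference the wait-list outcome. The shift *s* enters that arm in full, while the two exercise arms have masked post-tests.
- *Primary Aim 1 model*: 9.3.2 does not name Baseline 2. Section 8.2 moves second classes taught entirely by an exercise leader into Aim 1. Those participants have two baselines, and the plan does not say which is used.

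**4. How many people**

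Section 9.2 expects about 120 participants in Aim 2, and section 3 gives 400 in total: 120/400 = 30%. Participants in leader-led second classes also have a Baseline 2; their number is not given.

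**5. The 6MWT at the same visit**

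Section 6.1 repeats the 6MWT at Baseline 2. Sections 4.3 and 6.2.1.2 send an abnormal response to the primary care physician, but word this as a condition of enrolment, and these participants enrolled about 12 weeks earlier. The clearance rule in 8.1 is triggered by missed classes, so illness during the wait cannot trigger it.

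**The case against.** **The named uses are peripheral.** This stands. Aim 2 is exploratory and uses the first baseline; Baseline 2 replaces it only on repeat. The wait-list comparison is also a sensitivity analysis, and the role of Baseline 2 in it is inferred.

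**The text is silent on masking at baseline; it does not order unmasked testing.** This is fair as far as it goes. But the rule that 6.2.2 points to admits the coordinator, whom 7.5 calls unblinded, so a team following the plan as written could use an unmasked tester.

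**Masking can do only so much.** This stands in part. Only second-class participants have this visit, so its existence can reveal that someone waited, and participants may say so. Scheduling it with first-phase post-tests would hide this to some extent, and masking to programme remains possible.

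**The 6MWT rule already carries over.** This is largely right. The referral rule sits inside the baseline procedures that 6.2.2 adopts. Sections 5.4 (vital signs and ACSM stopping rules), 7.2 (monitored testing) and 8.2 (removal for unstable vital signs) give further cover. What is missing is a sentence stating what happens to someone already enrolled.

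**Stronger readings.** A reader might infer that the primary Aim 1 result is biased. The documents do not show that. It would require leader-led second classes to occur, Baseline 2 to be chosen for them, and either their share or the tester shift to differ between programmes. A reader might also try to work out how large a shift would inflate the error rate. The plan does not support this: the number of people waiting is not fixed, some could count in both the wait-list and an exercise arm, and neither of the protocol's design effects (1.90 between facilities, 0.90 for the paired comparison) fits a contrast that is partly within facility.

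**Conclusion.** The gap is real and should be closed. The protocol ties a post-randomisation measurement to a tester rule written for pre-randomisation visits. As a result, the Aim 2 sensitivity analysis and, by inference, the three-arm Aim 1 sensitivity analysis may compare unmasked with masked measurements. The sustainability and wait-list contrasts are the exposed ones; a common shift cancels in staff-led On the Move against Standard.

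The visit concerns about 30% of participants on the plan's own expectation, plus an unstated number in leader-led second classes. Neither the direction nor the size of any bias can be derived from the documents. The conclusion assumes that Baseline 2 supplies the wait-list outcome and that the team applies 10.1 as written. The 6MWT clearance and the choice of baseline for leader-led second classes are minor clarifications.

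**What to change.** **Main change, section 10.1.** Limit the pre-randomisation wording and the coordinator exception to screening and Baseline 1. Require Baseline 2 to be done by the masked assessors already used for post-intervention testing. Where possible, schedule it together with the first-phase post-tests, so that class assignment is also masked as far as is practical. The second class starts once the first has finished, so those assessors should be at the same sites at about that time.

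**Clarifications.**

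- Section 6.2.2: a Baseline 2 6MWT response that meets the section 4.3 thresholds needs physician clearance before the class starts. Anyone not cleared stays in follow-up and in the intention-to-treat analysis.
- Section 9.3.2: state which baseline applies to leader-led second classes counted in Aim 1.

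**Cost.** Low. The tests and the masked staff already exist. The change takes some scheduling effort, removes the coordinator as cover at Baseline 2, and may delay some participants' start while clearance is obtained. Masking to class assignment will remain partial.
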